### Statistical analysis

We will use descriptive analysis to report baseline characteristics. In this study the Repeated ANOVA between subjects test will be used for quantitative variables which have a normal distribution, and the Friedman test will be used for quantitative variables that do not have a normal distribution. For qualitative variables, chi-square test or Fisher’s exact test will be used. The effectiveness of the intervention will be assessed using the repeated measure ANOVA test and the effect of demographic variables on milk donation behavior will be determined using a logistic regression model. Statistical analyses will be made using IBM-SPSS 22. The trial has been registered at the Iranian Registry of Clinical Trials (IRCT20230124057203N1).

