### Sample size

In order to provide a power of 95% with 95% confidence interval the following formula and the standard deviation of 3.17 to 3.21 (according to the same study’s findings) will be used [18]. The sample size was estimated at 30, and then allowing for 10% attrition, we plan to recruit 33 samples per group and a total of 66 study participants.$$ n=\frac{{\left({z}_{1-\frac{\alpha }{2}}+{z}_{1-\beta }\right)}^{2}\left({s}_{1}^{2}+{s}_{2}^{2}\right)}{{\left({\overline{x}}_{1}-{\overline{x}}_{2}\right)}^{2}}$$$$ \frac{{\left(1.96+1.64\right)}^{2}\left({3.21}^{2}+{3.17}^{2}\right)}{{3}^{2}}=29.4\cong 30$$$$ 30+30\left(0.1\right)=33$$

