### Data collection

The questionnaire will be uploaded to Porsline, a well-known online survey platform in Iran, to create a link for the questionnaire. Participants can use their mobile phones to open the link and fill out the questionnaire. A baseline assessment will be conducted prior to the intervention for both the intervention and control groups. In order to assess the immediate and long-term effects of the intervention prospectively, the first follow up assessment will be conducted immediately after the intervention, and the final one will be conducted 12 weeks later. Our primary outcomes are the number of mothers who have donated their breast milk and changes that have happened in breastfeeding mothers’ knowledge, attitudes, subjective norms, perceived behavioral control about DHM and intention to donate milk. Our secondary outcomes are the associations of behavioral determinants and social demographic variables with milk donation.

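### The named between-subjects test of the repeated-measures ANOVA, taken literally, averages baseline into the arm comparison and does not estimate the change named as primary; the deciding effect should be stated

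*Protocol article*

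**What the plan says.** Three sections of the protocol article bear on this.

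- **Statistical analysis.** The test for normally distributed quantitative variables is given as follows: "the Repeated ANOVA between subjects test will be used for quantitative variables which have a normal distribution". Non-normal variables go to the Friedman test. A later sentence adds: "The effectiveness of the intervention will be assessed using the repeated measure ANOVA test". The section names no group-by-time term, no contrast at a follow-up visit and no baseline covariate.
- **Data collection.** There are three assessments. The first precedes treatment: "A baseline assessment will be conducted prior to the intervention for both the intervention and control groups". For the others, "the first follow up assessment will be conducted immediately after the intervention, and the final one will be conducted 12 weeks later". The primary outcomes include "changes that have happened in breastfeeding mothers", that is, change in knowledge, attitude, subjective norms, perceived behavioral control and intention.
- **Sample size.** The trial is sized for a plain difference of 3 points between two group means, using "the standard deviation of 3.17 to 3.21" and a power of 95%.

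**The concern.** In a repeated-measures ANOVA with arm as a factor, the between-subjects test is equivalent to a two-group comparison of each mother's average over all repeated levels. Baseline is measured before any teaching, so it can carry no intervention effect. If it is one of three levels, it takes a third of the weight and contributes nothing to the effect. The comparison is then of average level, not of change.

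Three things are at stake for the primary questionnaire outcomes. The reported arm difference would be smaller than the difference at follow-up. A difference between arms already present at baseline would be read as part of the effect. The sample size would no longer match the test, because it was computed for a difference that this test does not estimate. Baseline differences are a practical possibility: the Setting section allocates four centers per arm, and Recruitment takes mothers by convenience sampling.

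**Working it through.** **Inputs from the Sample size section.** SDs 3.21 and 3.17; difference 3; z-values 1.96 and 1.64; 30 per arm after the planned 10% attrition from 33. The section does not say which score the 3 points refer to, so I take it as a typical questionnaire score.

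**Assumed, not in the document.** The same SD at each assessment, the same correlation r between any two assessments (0.3 to 0.7 shown), the same effect d at both follow-ups, and clustering set aside.

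**1. The plan's own figure.** (1.96 + 1.64)² × (3.21² + 3.17²) / 3² = 12.96 × 20.353 / 9 = 29.31. The article prints 29.4; both round up to 30, and 30 × 1.1 = 33. The stated size reproduces. Pooled variance is 20.353 / 2 = 10.18, so SD = 3.19.

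**2. What the between-subjects test estimates.** With effects 0, d1 and d2 at the three assessments, the group effect is (0 + d1 + d2)/3. The mean follow-up effect is (d1 + d2)/2. The ratio is 2/3 whatever d1 and d2 are.
- 3 points at both follow-ups: (0 + 3 + 3)/3 = 2.
- 3 points fading to 1.5: (0 + 3 + 1.5)/3 = 1.5.

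A simulation of 10,000 trials at r = 0.5 gave a mean estimate of 1.99 for the first case.

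**3. Power for d = 3.** The variance of a plain difference in means is 2 × 10.18 / 30 = 0.678. Each analysis multiplies this by a factor. Noncentrality is effect / √(0.678 × factor), and power is from the noncentral t on 58 df, two-sided 5%.

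| Analysis | Effect | Variance factor | r = 0.3 | r = 0.5 | r = 0.7 |
|---|---|---|---|---|---|
| Between-subjects, three levels | 2 | (1 + 2r)/3 | 0.905 | 0.833 | 0.761 |
| One follow-up, unadjusted | 3 | 1 | 0.948 | 0.948 | 0.948 |
| One follow-up, baseline-adjusted | 3 | 1 − r² | 0.964 | 0.985 | 0.999 |
| Mean of both follow-ups, baseline-adjusted | 3 | (1 + r)/2 − r² | 0.998 | 0.999 | >0.999 |
| Mean of both follow-ups minus baseline | 3 | (1 + r)/2 + 1 − 2r | 0.938 | 0.985 | >0.999 |

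At r = 0.5 the noncentralities of the first four rows are 2.97, 3.64, 4.21 and 5.15. The simulated power of the between-subjects test was 0.829, in line with 0.833.

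The fourth row gains from averaging two visits as well as from adjustment. The fair measure of adjustment alone is the third row against the second: 0.985 against 0.948 at r = 0.5.

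**4. Where the power loss starts.** The between-subjects test matches the plain single follow-up comparison when 2/√((1 + 2r)/3) = 3, which gives 1 + 2r = 4/3, or r = 1/6. Below that correlation it has more power than the plain comparison; above it, less.

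**5. Realised baseline difference b.** It enters directly at b/3. With its expected carry-over rb to each follow-up, the shift is (b + 2rb)/3 = b(1 + 2r)/3, that is 0.53b, 0.67b and 0.80b at r = 0.3, 0.5 and 0.7. With baseline as covariate the expected shift is 0. The chance standard error of b is √0.678 = 0.82 points without clustering. A one-standard-error imbalance at r = 0.5 would therefore move the result by about 0.67 × 0.82 = 0.55 points.

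**The case against.** The strongest reply is that the wording is loose rather than wrong. The phrase can mean a repeated-measures ANOVA with arm as the between-subjects factor. The sentence on effectiveness refers to the repeated-measures ANOVA as a whole, which also yields a group-by-time test, and a primary outcome defined as change fits that test. The section also pairs the ANOVA with Friedman, a within-subject test that does not compare arms, so it appears to list families of tests rather than model terms. Nor does the article say outright that baseline is a repeated level. Detail of this kind often sits in a full protocol or analysis plan.

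Much of this stands, and it makes the dilution conditional. It does not remove the point. The article names one particular test, the between-subjects one, and that test does not match the outcome it is meant to serve. No sentence supplies the favorable reading. Three assessments are planned, and nothing says that baseline is left out or used as a covariate.

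Three stronger claims are tempting, and the documents do not support them.
- **That the between-subjects estimate is always less precise.** At r = 0.3 its variance factor is 1.6/3 = 0.533, against 0.65 − 0.09 = 0.56 for the baseline-adjusted mean of the follow-ups. Its power is lower there because the quantity estimated is smaller.
- **That baseline imbalance biases the method in general.** Chance imbalance under randomization averages to zero over repeated trials. The shift applies to a difference that has actually occurred, and the document gives no figure for how large that is likely to be.
- **That a third of the power is lost.** The third is lost from the estimate. Power falls by less, and not at all below r = 1/6.

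**Conclusion.** The point holds as a conditional one. Read literally, with baseline as one of the three levels, the named test gives two-thirds of the mean follow-up effect, 2 points where 3 were planned. It does not estimate change, and it keeps any realised baseline difference. The two-thirds ratio is algebra and needs no assumption about correlation.

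The power figures (0.91, 0.83 and 0.76 against 0.95) rest on assumed correlations, equal correlation between assessments, 30 per arm and no clustering. They compare analyses with one another. They are not forecasts for a trial with four centers per arm.

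A reader might infer that the trial will certainly report an effect shrunk by a third. The article does not establish that: if conclusions were drawn from group-by-time, or if only the two follow-ups were the repeated levels, the dilution would not arise. What is established is that the text names a test unsuited to the stated outcome and does not say which effect decides. Under either reading, adjusting follow-up scores for baseline improves on the stated test.

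**What to change.** In the Statistical analysis section, replace the reference to the between-subjects test with a statement of the effect that decides effectiveness. Preferably this is the arm difference in follow-up score with the baseline score as covariate, fitted in a way that respects allocation by center.

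If repeated-measures ANOVA is kept, state that the conclusion rests on the group-by-time contrast of follow-up against baseline and not on the between-subjects main effect. That contrast restores the full 3 points, but it responds to a realised baseline difference in the opposite direction, by (r − 1)b, or −0.5b at r = 0.5. The covariate form is therefore the better of the two.

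The cost is a change of analysis wording. Baseline is already collected in both arms, and no visit, questionnaire item or participant is added.

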**Methods:**

This cluster randomized controlled trial will be conducted in health centers affiliated to Tehran University of Medical Sciences and will enroll 66 breastfeeding mothers (intervention, *n* = 33; control, *n* = 33). After collecting baseline data, the intervention group will begin receiving a 60-minute weekly educational program based on Theory of Planned Behavior components for four weeks. The first follow-up assessment will be conducted immediately after the intervention, and the final one will be conducted 12 weeks later. The primary outcomes are the number of mothers who have donated their breast milk and changes in breastfeeding mothers’ knowledge, attitude, subjective norms, and perceived behavioral control about donor human milk and intention to donate milk.

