## Methods

### Study design

A cluster randomized controlled trial will be carried out on breastfeeding mothers referred to health centers affiliated to Tehran University of Medical Sciences. A cluster randomized controlled trial design was chosen because it makes it easier for mothers to attend classes at their local health center, and in this design, the phenomenon of contamination between the intervention and control groups is avoided. Besides, it can help us increase the representativeness and generalizability of our study population and results. The control group allows us to analyze the direct effect of the intervention and discount an increase in milk donation due to other factors [20]. This study was approved by the Research Ethics Committees of School of Nursing and Midwifery & Rehabilitation - Tehran University of Medical Sciences (IR.TUMS.FNM.REC.1401.150).

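### The Friedman test named for non-normal scores has no between-arm term and conflicts with the plan's own statement of how effectiveness will be tested

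*Protocol article*

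**What the plan says.** The Statistical analysis section of the protocol article sorts quantitative variables by distribution. For the normal ones, "the Repeated ANOVA between subjects test will be used for quantitative variables which have a normal distribution"; for the rest, "the Friedman test will be used for quantitative variables that do not have a normal distribution". Categorical variables are handled separately: "For qualitative variables, chi-square test or Fisher’s exact test will be used". The section then adds, with no condition on distribution, "The effectiveness of the intervention will be assessed using the repeated measure ANOVA test". Logistic regression is named only for the effect of demographic variables on donation. No rank-based comparison between arms is named anywhere.

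Under Data collection, the primary outcomes are the number of mothers who donated and "changes that have happened in breastfeeding mothers’ knowledge, attitudes, subjective norms, perceived behavioral control about DHM and intention to donate milk". There are three assessments: one at baseline, and then "the first follow up assessment will be conducted immediately after the intervention, and the final one will be conducted 12 weeks later".

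**The concern.** The two tests are presented as counterparts, but they answer different questions. A repeated measures ANOVA with a between-subjects factor can ask whether the arms differ, or whether they change differently over time. Friedman's test asks only whether one set of subjects changes over time.

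If a primary score is judged non-normal and the rule is followed, the reported p-value says nothing about intervention against control. A rise shared by both arms, for example from answering the same questionnaire three times, could be credited to the program. A real difference between arms could also be missed when all mothers are pooled. The sample size is built on a difference between two group means, so on this branch the analysis would not match the comparison the trial was sized for.

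**Working it through.** **1. The comparison the trial was sized for.** Inputs from Sample size: z-values 1.96 and 1.64, SDs 3.21 and 3.17, difference 3.

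n = (1.96 + 1.64)² × (3.21² + 3.17²) / 3² = 12.96 × (10.3041 + 10.0489) / 9 = 12.96 × 20.353 / 9 = 29.3

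The article prints 29.4; both round up to 30. With its 10% allowance, 30 + 3 = 33 per group and 66 in total. The planned size is reproduced, and it rests on a difference between arms.

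**2. What Friedman's test uses.** Each mother's three values are ranked 1 to 3 against each other, and the rank sums are compared across the three times. Arm does not enter. Run on all mothers, it tests time only. Run within each arm, it gives two separate before-after tests.

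**3. The sentences side by side.**
- The distribution rule sends normal scores to ANOVA and non-normal scores to Friedman.
- The effectiveness sentence sends effectiveness to ANOVA, without a condition.
- For a non-normal score these cannot both give the test of effectiveness. If the rule governs, there is no between-arm test. If the effectiveness sentence governs, the rule's restriction of ANOVA is set aside and Friedman's role is undefined.

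**4. Illustration: no intervention effect, same rise in both arms.** 33 mothers per arm, three times, the same rise at both follow-ups, 5% level. The size of the rise and the within-mother correlation of 0.5 are assumptions; neither is in the article. Scores were simulated as normal. Because Friedman uses only within-mother ranks, a strictly increasing transformation of all scores, skewed or not, would leave its results unchanged.

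| Share of trials significant | 0.2 SD | 0.3 SD | 0.5 SD |
|---|---|---|---|
| Friedman, all mothers | 26% | 54% | 96% |
| Friedman, intervention arm alone | 14% | 30% | 68% |
| Intervention arm significant, control arm not | 12% | 21% | 20% |
| Between-arm rank test on change scores | about 5% | about 5% | about 5% |

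For a 0.5 SD rise, the intervention-arm rate is about 54% at a correlation of 0.3 and about 90% at 0.7. The third row follows from the second: with independent arms and equal rates p, it is p(1 − p), for example 0.68 × 0.32 = 0.22 against about 0.20 simulated.

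**5. The opposite error.** 30 mothers per arm, SD 3.19, correlation 0.5 (assumed), and the planned 3-point difference split as +1.5 in one arm and −1.5 in the other. Friedman on all mothers rejects in 3.2% of trials; a between-arm rank test on change rejects in 93%. This even split is chosen to show that the test does not see arm. With +3 against 0, pooled Friedman rejects in 82% because of the overall movement in time, and the between-arm rank test in 94%.

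Steps 4 and 5 ignore clustering by health center, which is a separate matter.

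**The case against.** The strongest reply is the effectiveness sentence itself. It has no normality condition, so one plain reading is that ANOVA tests effectiveness for every score and Friedman only describes change over time. That reading is available. It stands to this extent: one cannot say flatly that non-normal outcomes get no test of the intervention. It does not remove the problem, because it contradicts the rule two sentences earlier, and the article does not say which governs.

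Four stronger readings are tempting, and the article does not support them:

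- *The control group is never used.* Donation yes/no goes to chi-square or Fisher's exact test, and normally distributed scores go to the between-subjects ANOVA. The Study design sentence that the "The control group allows us to analyze the direct effect of the intervention and discount an increase in milk donation due to other factors" speaks of milk donation, whose primary form is binary and never reaches Friedman.
- *The number of donations is an affected primary outcome.* The primary outcome is the number of mothers who donated. Times donated is a questionnaire item only.
- *The scores will be skewed.* The article gives no distributions. Bounded scores from multiple-choice and 5-point items, with about 33 mothers per arm, may well fail a normality check, but that is a judgment.
- *The false-positive rate is 68%.* That is a one-arm rate for one assumed rise. If an effect is claimed only when the intervention arm is significant and the control arm is not, the rate is about 12% to 21%, which is still well above 5%.

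**Conclusion.** The concern holds in a limited form. The plan names a within-subject test as the counterpart of a between-subjects ANOVA, and this clashes with its own effectiveness sentence. For any of the five primary scores judged non-normal, either there is no controlled comparison, or the test of effectiveness is undetermined until the data have been seen. This is a method stated wrongly, not a detail left to a fuller document.

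How much it matters depends on how many scores take the non-normal branch, which is unknown, and on how the Friedman results would be read. Under the assumed common rises, false claims run from about 12% (the two arms' results contrasted) to 96% (all mothers pooled), against a nominal 5%. The sample size calculation is not affected.

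**What to change.** Remove Friedman as a test of effectiveness; at most, keep it as a within-arm description of change. State that the effect on every quantitative outcome is tested by a between-arm comparison, and reconcile the distribution rule with the effectiveness sentence. For non-normal scores, name a between-arm rank or permutation test on change or on baseline-adjusted follow-up values, built to respect the randomized health centers.

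The cost is a small amount of analysis wording; recruitment and data collection do not change. One consequence should be stated. Eight centers split four and four give 70 allocations, so a permutation test over centers has a smallest two-sided p of 2/70 = 0.029. Its power is also below the individual-level figure. With a difference of 3, SD 3.19 and no baseline adjustment, simulation gave about 70% with no clustering and 58% at an assumed intraclass correlation of 0.05, against the planned 95%. Baseline adjustment would recover part of that.

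### The repeated-measures ANOVA discards the observed scores of any mother who misses one assessment; that loss of data is certain, but bias is conditional and probably small

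*Protocol article*

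**What the plan says.** The Data collection section sets three assessments. The first is before the program: "A baseline assessment will be conducted prior to the intervention for both the intervention and control groups". For the other two, "the first follow up assessment will be conducted immediately after the intervention, and the final one will be conducted 12 weeks later". Alongside the number of donors, the primary outcomes are "changes that have happened in breastfeeding mothers’ knowledge, attitudes, subjective norms, perceived behavioral control about DHM and intention to donate milk".

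The Statistical analysis section names the method and the software. For normally distributed scores, "the Repeated ANOVA between subjects test will be used for quantitative variables which have a normal distribution"; otherwise "the Friedman test will be used for quantitative variables that do not have a normal distribution". It then states that "The effectiveness of the intervention will be assessed using the repeated measure ANOVA test" and that "Statistical analyses will be made using IBM-SPSS 22".

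The Sample size section arrives at 30 per group and then, "allowing for 10% attrition", recruits 33. The article gives no imputation step, mixed model or other rule for a mother with one missing assessment.

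**The concern.** A classical repeated-measures ANOVA needs a score at every level of the within-subject factor, and SPSS drops incomplete cases listwise. The Friedman test also needs complete rows. So a mother who answers at baseline and after the fourth session, but does not open the week-12 link, leaves the whole analysis. Her post-program score, a primary outcome that was observed, is not used.

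Two things are at stake. One is waste: data already collected are discarded. The other is a shift in the question answered, from the effect in the breastfeeding mothers enrolled (Objectives section) to the effect in those who completed all three questionnaires. The two can differ if the reasons for not answering differ between arms. That is conceivable, because intervention mothers attend four sessions promoting donation and controls receive only usual education.

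The point covers the five scores. It does not cover the donation count, which is a qualitative variable assigned to chi-square, Fisher's exact test or logistic regression. It is also separate from the exclusion criteria in the Recruitment section: with all of those removed, the named procedures would still drop incomplete cases.

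**Working it through.** **Inputs from the plan (Sample size section).** SDs 3.21 and 3.17; difference 3; z-values 1.96 and 1.64; 10% attrition; 33 per group. Pooled SD = sqrt((3.21² + 3.17²)/2) = 3.19.

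**Assumed, not in the plan.** Loss occurs between the post-program and week-12 assessments. The correlation between any two assessments is the same, 0.5 or 0.7. The dropout mechanisms are those described below.

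**1. The plan's own figure.** (1.96 + 1.64)² × (3.21² + 3.17²)/3² = 29.31, rounded up to 30. The article prints 29.4, a trivial difference. Then 30 × 1.1 = 33.

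**2. Mothers kept.** At 10% loss, complete rows leave 33 × 0.9 = 29.7 per group, about 59 of 66. About 7 mothers with observed baseline and post-program scores are discarded.

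**3. Power, by the plan's formula.** It is 96.9% with 33 per group, 95.4% with 30 and 95.2% with 29.7. The variance of the post-program contrast rises by 33/30 = 1.10, so its SE rises by sqrt(1.10) = 1.049, about 5%. The stated 95% is kept.

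**4. Bias in the raw post-program contrast.** Let 10% of intervention mothers be lost with a logistic probability that depends on the post-program score, and let loss in controls be unrelated to score. The mean of those retained then shifts upward:

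- odds ratio 2 per SD lower score: 0.21 points (7% of 3);
- odds ratio 3: 0.31 points (10% of 3);
- extreme case, exactly the lowest 10% lost: 3.19 × 0.1755/0.9 = 0.62 points.

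**5. Bias in change from baseline.** The outcomes are defined as changes, and the arm-by-time test compares changes. Those retained because of a high post-program score also had higher baselines on average, by the shift times the correlation. The bias in change is therefore shift × (1 − correlation).

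| Mechanism (intervention arm only) | Raw, post-program | Change, correlation 0.5 | Change, correlation 0.7 |
|---|---|---|---|
| Odds ratio 2 | 0.21 | 0.11 | 0.06 |
| Odds ratio 3 | 0.31 | 0.16 | 0.09 |
| Lowest 10% lost | 0.62 | 0.31 | 0.19 |

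For odds ratios 2 to 3 this is 0.06 to 0.16 points, or 2% to 5% of 3.

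**6. Week 12.** The raw week-12 shift is the post-program shift times the correlation. The baseline shift is the same amount when correlations are equal, so the bias in the week-12 change is about zero.

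**7. Other mechanisms.** A simulation with 33 per group and 4,000 runs returned 3.0 for a true effect of 3 at both follow-ups when 10% loss was random, and 3.0 again (to within 0.01) when loss was score-related equally in both arms.

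**The case against.** The strongest defense has four parts.

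*The bias is speculative.* It needs score-related loss in one arm and not in the other, which nothing in the article establishes. If low-scoring controls were the ones to leave, the sign would reverse. This stands. A reader might infer that the ANOVA inflates the program effect at both follow-ups by 7% to 10% or more. The documents do not support that: figures of that size belong to the raw post-program score, whereas the outcomes are changes, for which the overstatement is much smaller and about zero at week 12. Even the raw 0.21 to 0.31 is only about a quarter to two-fifths of the SE of the difference at 30 per group, 3.19 × sqrt(2/30) = 0.82.

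*The precision loss is already paid for.* This also stands. The increase from 30 to 33 covers 10% attrition, so a claim that the trial loses its stated power would be wrong at that rate. Two independent losses of 10% would leave 33 × 0.81 = 26.7 per group, but the plan does not describe that situation.

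*Missing-data handling belongs in the analysis plan, and listwise deletion is nowhere stated.* This stands in part. Deletion is inferred from the named procedures and would not follow if imputation came first. But the article does more than leave a gap: it fixes an estimator and software that suit complete data while expecting incomplete data.

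*A mixed model is no cure-all.* True. If loss follows a mother's own gain and not her score, the cancellation in step 5 is weaker. For example, if the lost 10% gained nothing and completers gained 3, the effect in all mothers would be 0.9 × 3 = 2.7. A mixed model uses the observed post-program scores in full, but would close only part of that gap at week 12.

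**Conclusion.** The point holds as a poorly chosen method for the five primary scores. Under the named procedures, and with no imputation stated, every mother who misses one assessment loses the scores she did provide: about 7 of 66 at the planned attrition. That follows whatever the reason for loss.

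Bias does not follow automatically. It is about zero under random loss or loss equally score-related in both arms. It is 0.06 to 0.16 points in the post-program change, and about zero in the week-12 change, if score-related loss is confined to the intervention arm. Those figures rest on assumed odds ratios of 2 to 3 per SD, equal correlations of 0.5 to 0.7, and 10% loss after the post-program assessment. Power by the plan's own formula stays near 95%. The case for changing the method is that observed primary data are discarded for no gain, some bias is possible, and the better method costs little.

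**What to change.** In the Statistical analysis section, replace the repeated-measures ANOVA and its Friedman alternative for the five scores with a likelihood-based linear mixed model (the MIXED procedure in SPSS). Specify:

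- fixed effects for time, arm and arm-by-time;
- correlated repeated measures within mother;
- a random effect for health center with small-sample degrees of freedom, because the Setting section allocates eight centers, four per arm;
- use of every available score, with arm contrasts reported at the post-program and 12-week assessments.

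State that a missed assessment alone does not remove a mother. Align this with the Recruitment section, where the exclusion for leaving more than 20% of the questionnaire unanswered could be read to cover an unopened week-12 link. Keep the complete-case ANOVA as a sensitivity analysis.

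The cost is a short rewrite and slightly more analysis work in the same software, with no extra mothers or data. The model relies on scores being missing at random, which is still an assumption but a weaker one than the missing-completely-at-random assumption behind the ANOVA.
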